## Abstract

**Background:**

Depression is one of the most common disorders in Psychiatric and Primary Care settings and is associated with significant disability and economic costs. Low-intensity psychological interventions applied by Information and Communication Technologies (ICTs) could be an efficacious and cost-effective therapeutic option for the treatment of depression. The aim of this study is to assess 3 low-intensity psychological interventions applied by ICTs (healthy lifestyle, positive affect and mindfulness) in Primary Care; significant efficacy for depression treatment has previously showed in specialized clinical settings by those interventions, but ICTs were not used.

**Method:**

Multicenter controlled randomized clinical trial in 4 parallel groups. Interventions have been designed and on-line device adaptation has been carried out. Subsequently, the randomized controlled clinical trial will be conducted. A sample of N = 240 mild and moderate depressed patients will be recruited and assessed in Primary Care settings. Patients will be randomly assigned to a) healthy lifestyle psychoeducational program + improved primary care usual treatment (ITAU), b) focused program on positive affect promotion + ITAU c) mindfulness + ITAU or d) ITAU. The intervention format will be one face to face session and four ICTs on-line modules. Patients will be diagnosed with MINI psychiatric interview. Main outcome will be PHQ-9 score. They will be also assessed by SF-12 Health Survey, Client Service Receipt Inventory, EuroQoL-5D questionnaire, Positive and Negative Affect Scale, Five Facet Mindfulness Questionnaire and the Pemberton Happiness Index. Patients will be assessed at baseline, post, 6 and 12 post-treatment months. An intention to treat and per protocol analysis will be performed.

**Discussion:**

Low-intensity psychological interventions applied by Information and Communication Technologies have been not used before in Spain and could be an efficacious and cost-effective therapeutic option for depression treatment. The strength of the study is that it is the first multicenter controlled randomized clinical trial of three low intensity and self-guided interventions applied by ICTs (healthy lifestyle psychoeducational program; focused program on positive affect promotion and brief intervention based on mindfulness) in Primary Care settings.

**Trial registration:**

Current Controlled Trials ISRCTN82388279. Registered 16 April 2014.

## Background

Depression is one of the most common disorders in Psychiatric and Primary Care settings [1] and is associated with significant physical comorbidity [2,3] disability and economic costs [4]. According to the World Health Organization, this disorder will become the second most important cause of disability in 2020 [5]. Previous studies reported that in Spanish Primary Care, depression prevalence is between 13.9 and 29% [1,6] and 60% of patients with depression are attended in a Primary Care Center [7]. Although general practitioners refer only 5-10% of the patients with psychiatric disorders to specialized services [8], mental health services are collapsed all over occidental countries.

There is strong evidence that pharmacotherapy and psychotherapy could be the first-line treatment for depression [9,10]. Although a combination of both have been shown the best option [11], pharmacotherapy is the most common intervention in primary care settings [12], even though relapse is high following cessation, and many patients prefer psychological therapies [13]. In the last decades, there has been a growing interest and commitment to integrate psychotherapy and other mental health services in Primary Care [14]. However, to date this type of treatment is not being used proportionate in Primary Care. Different factors as professional’s training, time needed, costs or work overload, professional’s attitudes and organization, geographical and logistic difficulties may contribute to it. An important goal in Primary Care is that the patient could choose psychological treatment for different reasons: There are patients that would prefer psychotherapy rather than pharmacologic treatment [15,16], and there is a need to offer alternative treatments to the patients that do not respond or respond partially to antidepressants and can benefit from the psychotherapy in terms of costs and relapse prevention [17].

One of the most important difficulties to integrate psychotherapy in Primary Care is lack of time. Many treatment protocols, with empirical support, last one hour weekly during 12-16 sessions. Lack of time and resources suppose important difficulties to the application of this type of therapy. For these reasons, brief psychotherapy for depression is an efficacious alternative [18]. Because of the efficacy of these interventions [10,19,20] and the challenge that depression suppose to the health system, nationals and internationals clinical guides [9,10,21] have proposed a “stepped care” treatment model in Primary Care by which large proportion of patients is treated with significant clinical benefits. This therapy is easier and simpler than formal psychotherapy and it can be used with nontraditional methods such as internet or mobile phones. In depressive patients, low-intensity interventions are recommended to mild and moderate depressive patients. The main interventions are: Cognitive behavior therapy (CBT), Computerized Cognitive Behavior Therapy (CCBT), Self-help programs, Psychoeducational Interventions and mindfulness-based cognitive therapy (MBCT).

Previous research suggests that not all depressed primary care patients are receiving adequate treatment for depression [22] therefore, there is an urgent need to change the way to deliver psychological interventions. There are recommendations regarding going beyond face-to-face psychotherapy in order to improve the accessibility to psychological interventions [23]. In this sense, in the last years, low-intensity psychological interventions applied by Information and Communication Technologies (ICTs) have been shown as an efficacious therapeutic option for the treatment of many mental health problems, including depression. In fact, different meta-analysis have demonstrated that Internet-delivered psychotherapy (iPT) is effective in the treatment of depression [20,24].

Due to the interest about on-line psychotherapy and the need to cover therapeutic management of depressive patients, different European research groups have designed computerized programs for depression prevention and treatment.

Proudfoot and colleagues [25] developed a computerized cognitive behavioral therapy to mild and moderate depression named “Beating the Blues”. It is the most used program and the only computerized treatment program recommended by NICE for the treatment of people with this type of disorder at the moment. Another interactive program based on CCBT is the MoodGym program [26] from the Australian National University, developed to depression prevention [27]. In Spain, there is only one computerized program based on CCBT to depression management in primary care setting [28]. At the present, the study is being conducted by our research group and results will be presented soon.

Considering that low-intensity psychological interventions applied by Information and Communication Technologies (ICTs) could be an efficacious and cost-effective therapeutic option for the treatment of depression, the aim of the present study will be to assess three low-intensity psychological interventions (healthy lifestyle psychoeducational program, focused program on positive affect promotion and brief intervention based on mindfulness) applied by ICTs in Primary Care.

## Methods

### Study design

This is a multicenter controlled randomized clinical trial in four parallel groups: a) healthy lifestyle psychoeducational program, b) focused program on positive affect promotion, c) brief intervention based on mindfulness and d) improved treatment as usual (ITAU) group in primary care.

### Setting and study sample

The recruitment strategy will be performed by General Practitioners (GPs) from primary health centers of the four Spanish regions involved in the study (Andalucía, Aragon, Islas Baleares and Comunidad Valenciana). Inclusion criteria are: older than 18 years, DSM-5 diagnose of Major Depression or Dysthymia, mild or moderate depression expressed as score lower than 14 in the Patient Health Questionnaire (PHQ) [29], depressive symptoms presented for at least two months, be able to read and understand Spanish language and enough capacity for understanding and signing the written informed consent form. Exclusion criteria includes any diagnose of disease that may affect central nervous system (brain pathology, traumatic brain injury, dementia, etc.), any psychiatric disorder other than Major Depression, Dysthymia, anxiety disorders or personality disorders, any medical, infectious or degenerative disease that may affect mood, presence of delusional ideas or hallucinations consistent or not with mood, and suicide risk.

### Sample size

According to the literature, with a standard deviation (SD) of 9.2 and a mean of 16.2 in the control group (ITAU) [30], 14.59 in the positive affect group [31], 16.12 in the healthy lifestyle group [32] and 10.3 in the mindfulness group [30], accepting an alpha of 0.05 and a beta risk < 0.2 in a bilateral contrast, and assuming a 25% patient loss to follow-up, we need 60 subjects in each condition. Therefore, the total sample size was determined at 240. This sample size also allows calculating clinically significant difference in the main outcome variable, PHQ-9 [29], and this difference has been placed at 5 points.

### Recruitment

The recruitment strategy will be performed in primary care settings by participating GPs among patients fulfilling study criteria. When the GP identifies a potential participant, he/she will explain the patient the characteristics of the study. Whether the patient is interested in participating he/she will sign an informed consent and the GP will fill a referral form describing the sociodemographic characteristics of the patient and a checklist for inclusion/exclusion criteria, and will give him/her the patient’s information sheet and a handout describing the study. If the patient does not want to participate or does not meet inclusion criteria, the GP will fill the referral form describing the reason for not including him/her. The GP will send these documents by fax to the local researcher. Subjects will be interviewed in the next 3 days by the researcher. After confirming that they have signed the informed consent and have understood the study and the treatment options, the researcher will administer the psychological assessment instruments related with inclusion criteria: MINI International Neuropsychiatric Interview [33], PHQ-9 [29] and sociodemographic variables. The researcher will collect baseline data and will contact an independent researcher to implement the randomization.

### Randomization, allocation and masking of study groups

Each patient will be allocated to either one of the four groups using a computer-generated random number sequence. We will use block allocation, with 4 blocks (one for each participating region) including 60 patients per block, with about 60 patients per arm. The allocation will be carried out by an independent researcher, belonging to REDIAPP (Research Network on Preventative Activities and Health Promotion), who is not involved in the study. The method used to implement the random allocation sequence will be a central telephone. The sequence will be concealed until interventions are assigned. Patients will agree to participate before the random allocation and without knowing which treatment they will be allocated to. Study personnel conducting psychological assessments will be masked to participants’ treatment conditions.

The researcher that administers baseline assessments will be unaware of the treatment group to which the patient belongs to. This researcher will be different from the one that administer the questionnaires over the study. GPs will be also unaware, as long as possible, of the arm to which the patient has been randomized, since their treatment should be exclusively based on the recommendations of the guides for the treatment of depression. The flowchart of the study is summarized in Figure 1.

**Figure 1 Fig1:**
[figure not shown]
Flowchart of the study: Randomization, sampling and monitoring of patients.

### Interventions

All interventions (except ITAU) are composed of one face-to-face group session and 4 online, individual and interactive therapeutic modules.

Face-to-face session will involve 3-5 patients and will be 90 minutes in length. The aim of this session will be to explain the program structure and main components of treatment, and to motivate participants for change.

The online therapeutic modules are oriented to work on different psychological techniques and the duration of each module will be approximately 60 minutes. All modules include an explanation of the module contents, check questions to test if they understand the contents and exercises to practice such techniques. These modules are sequential, in order to move step by step, all along the program. However, user can review the module contents once they are finished. Duration of the program can vary among users, it is estimated the duration for most people will be 4-8 weeks. The participants will receive two weekly-automated mobile phone messages, encouraging them to proceed with the program and reminding them of the importance of doing the tasks in each module. Furthermore, the participants will receive an automated e-mail encouraging them to continue with the modules if they have not accessed the program for a week. The program also offers continued feedback to users through the assessment tools showing them their progress throughout the entire treatment process.

All groups of patients will receive treatment as usual improved by their GPs, as described below in this section. All groups of patients will also receive a participant manual with information about technical aspects of the online program.

#### Psychoeducational program for the promotion of a healthy lifestyle

This program provides information to understand the relationship between physical and mental health and physical activity, diet and sleep control.

The content of the program is the following:***M1****.****Beginning of a lifestyle change***: This module aims to teach the importance of healthy lifestyle to improve emotional health and general well-being and to give structured hygienic-dietary recommendations. The patient will learn to identify both healthy and risk behaviors, and to recognize the most common obstacles that prevent the depressed patients from adopting a healthy lifestyle.***M2****.****Physical activity****.****Learning to move on****:* This module focuses on behavior activation by teaching the importance of “moving on” and taking regular exercise to improve mood. In this module the main aim is to give information about the most recommended exercises to improve mood, and to train the patient in learning procedures to increase the motivation, to start being more active, and to maintain this physical regularly.***M3****.****Diet****.****Learning to eat****:* This module is devoted to teach the importance of diet to achieve a good physical and mental health, and the role of the Mediterranean diet in the prevention and treatment of depression. For this purpose the obstacles to maintain a healthy diet will be analyzed.***M4****.****Sleep****.****The importance of good sleep****:* This module provides information to understand the relationship between sleep and general health. The patient will be trained to develop strategies to improve sleep.

#### Psychological intervention for the promotion of positive affect

The purpose of this program is to decrease depressive symptomatology and to prevent relapses using the promotion of wellbeing and positive affect.

The content of the program is the following:***M1****.****Learning to live****:* The first module is dedicated to the importance of establishing and maintaining an adequate activity level and the relevance of choosing activities which are significant, with a personal meaning for the individual. The content will cover also the importance of social support in order to make easier the task of establishing meaningful activities. The patient will be trained to carry out and monitor meaningful activities using a therapeutic tool, the activity diary.***M2****.****Learning to enjoy****:* In this module the main aim is to give education about the effect of positive emotions and to train the patient in learning procedures to increase the likelihood of experiencing positive emotions, promoting the occurrence of pleasant activities in order to learn to enjoy the present moment.***M3****.****Accepting to live****:* In the previous module the focus was in positive emotions related with the present time. In this module the patient will be trained in focusing in positive emotions related with the past (like gratitude) or the future (like optimism). This module also deals with the identification and management of beliefs and behaviors that disturb the good moments.***M4****.****Living and learning****:* The aim of this module is to train the patient in understanding life as a continuous process of learning and personal growth, emphasizing the training in strategies to promote psychological strengths, resilience and meaningful goals linked to important values. The content of the module will also include understanding the effort needed in order to achieve a meaningful life, helping the patient to make a plan for the future to achieve his/her life goals.

#### Brief intervention based on mindfulness

This program, which aim is to decrease depressive symptomatology using mindfulness, emphasizing the benefits of this therapy.

The content of the program is the following:***M1****.****Getting to know mindfulness***: This module aims to show what mindfulness is, prejudices about it, the inattention problem and some of its main benefits and recommendations to practice it. Finally, a mindful practice (the raisin exercise) will be shown.***M2****.****Establishing formal and informal practices****:* In this module it will be raised the importance of the establishment not only of formal but also of informal practice. For this purpose different techniques such as the three minutes practice will be shown.***M3****.****Thought management****,****body scan practice and values****:* This module aims to help people to see the importance of values to keep a regular mindfulness practice. It also will include the body scan practice.***M4****.****Self****-****compassion****.****Integrating mindfulness in everyday life****:* This module will help people to establish a regular practice of mindfulness to be indefinitely kept. It also will include a very powerful practice, self-compassion, which has shown efficacy by itself [27].

#### Improved treatment as usual (ITAU)

All the patients included in the study (whatever the treatment group randomly assigned) will be also treated by their GPs. The Treatment as Usual in primary care will be improved because the participating GP will receive a training program on a widely used Spanish Guide for the Treatment of Depression in Primary Care [7]. In case of suicide risk, severe social dysfunction or worsening of symptoms, it is recommended to refer the patient to mental health facilities. In practice, ITAU in primary care is any kind of treatment administered by the GP to the patient with depression.

### Instruments

Patients will be assessed at baseline, post-treatment, and 6 and 12 post-treatment months. The study variables assessed are summarized in Table 1.

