**Table 1 Tab1:** **Study variables**

**Instrument**	**Assessment area**	**Time of assessment**	**Applied by**
MINI Neuropsychiatric interview	Psychiatric diagnosis	Baseline	Researcher A
PHQ-9	Severity of depression	Baseline and follow-up sessions*	Researcher A (baseline) Online (follow-up sessions)
Sociodemographic data	Gender, age, marital status, education, occupation, economical level	Baseline	Researcher A
SF-12 Health Survey	Health-related quality of life	Baseline and follow-up sessions*	Online
CRSI	Health and social services use	Baseline and 6 and 12 post-treatment months	Researcher A (baseline) Researcher B (6 and 12 post-treatment months)
EQ-5D	Health related quality of life	Baseline and 6 and 12 post-treatment months	Online
PANAS	Positive and negative affect	Baseline and 6 and 12 post-treatment months	Online
FFMQ	Facets and factors of mindfulness	Baseline and 6 and 12 post-treatment months	Online
PHI	Remembered and experienced well-being	Baseline and 6 and 12 post-treatment months	Online

*Follow-up sessions: Post-treatment, 6 and 12 post-treatment months.

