#### Main outcome

The primary outcome will be depressive symptom severity assessed via PHQ-9 [34] using the Spanish validated version [29]. This is an instrument for diagnosis and measuring the severity of depression. PHQ-9 is brief and it is completed by the patient. It will be registered at four times: baseline, post-treatment, 6 month follow-up, and 12 month follow-up.

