### Forecast execution dates

Initial recruitment of patients: February 2015

Finalization of patient recruitment: July 2015

Finalization of patient monitoring period: July 2016

Publication of results: December 2016

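### Follow-up is anchored to a post-treatment date that varies by user in the active arms and does not exist in ITAU, and the July 2016 close leaves no room for the programme among late recruits

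*Protocol article*

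**What the plan says.** The Instruments section gives one schedule for all patients: "Patients will be assessed at baseline, post-treatment, and 6 and 12 post-treatment months". The footnote to Table 1 repeats it: "Follow-up sessions: Post-treatment, 6 and 12 post-treatment months". The Main outcome section lists the PHQ-9 times as "baseline, post-treatment, 6 month follow-up, and 12 month follow-up" and does not say what the 6 and 12 months are counted from.

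The Interventions section says "Duration of the program can vary among users" and adds that "it is estimated the duration for most people will be 4-8 weeks". It states no maximum. The same section excludes ITAU from the group session and the online modules. The ITAU section describes that arm as whatever treatment the GP gives, with no end point.

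Forecast execution dates puts the start of recruitment in February 2015 and its end in July 2015, and then states "Finalization of patient monitoring period: July 2016". Analysis perspective and time horizon sets a 12-month horizon for the economic analysis.

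**The concern.** A randomised comparison of symptom scores needs the same time zero in every arm. Here the stated time zero is an event after randomisation that the patient's own pace determines in three arms and that has no counterpart in the fourth. Patients who stop the modules early have no end-of-treatment date either. They are unlikely to be few: the Discussion expects more dropout in the treatment groups than in control and aims to hold it to around 30%, and some of that dropout will presumably be stopping the modules.

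Depression scores can change with time whether or not a programme is given. If elapsed time differs between arms, part of any PHQ-9 difference could reflect the timing of the visit. This bears on the intention-to-treat, head-to-head comparison of the four groups that the Analysis strategy promises, and the timing cannot be put right once the data are collected.

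The second issue is the calendar. If the 12 months run from the end of treatment, patients recruited late have their last visit due after monitoring ends. The 12-month economic horizon also fits counting from entry better than counting from the end of treatment.

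**Working it through.** **Inputs from the protocol article.** Programme 4-8 weeks for most users (Interventions); visits at post-treatment and 6 and 12 months later (Instruments, Table 1); recruitment February to July 2015 and monitoring to July 2016 (Forecast execution dates); 60 per arm (Sample size), so 3 × 60 = 180 active-arm patients.

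**Assumptions not in the document.** Uniform accrual; recruitment, randomisation and programme start on the same day, with no wait for the group session; specific days within the stated months.

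**1. The plan's own closing date.** July 2015 + 12 months = July 2016. This reproduces the stated close, but with 0 weeks for the programme. Counting 12 months from the end of treatment for the last recruit reproduces it in only one favourable corner: last patient on 1 July 2015, a 4-week programme, no wait, close on 31 July 2016 (visit due 29 July 2016).

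**2. Elapsed time in the active arms, from programme start.**
- Post-treatment visit: 4 to 8 weeks.
- 6-month visit: 26 + 4 = 30 to 26 + 8 = 34 weeks.
- 12-month visit: 52 + 4 = 56 to 52 + 8 = 60 weeks.

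That is a 4-week spread between patients, wider for anyone slower than 8 weeks.

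**3. Gap to ITAU.** It depends on an anchor that the article does not give.
- ITAU timed from randomisation: 56 − 52 = 4 to 60 − 52 = 8 weeks, and the same at 6 months.
- ITAU given a nominal 4-week date: active patients are 0-4 weeks later. With a nominal 8-week date they are 0-4 weeks earlier.

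**4. Last visit of the last recruit.** 31 July 2015 + 28 days + 12 months = 28 August 2016. 31 July 2015 + 56 days + 12 months = 25 September 2016. These are 28 and 56 days after a 31 July 2016 close. Visits fit only for patients recruited by 3 July 2015 (4 weeks), 19 June (6 weeks) or 5 June (8 weeks).

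**5. Share of visits due after the close.** Share = days by which the last recruit overruns ÷ days of recruitment, starting 1 February 2015 (181 days to 31 July, 151 days to 1 July).

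| Last recruit | Close | 4 weeks | 6 weeks | 8 weeks |
|---|---|---|---|---|
| 31 July 2015 | 31 July 2016 | 28/181 = 15.5% | 42/181 = 23.2% | 56/181 = 30.9% |
| 1 July 2015 | 31 July 2016 | 0% | 12/151 = 7.9% | 26/151 = 17.2% |
| 1 July 2015 | 1 July 2016 | 28/151 = 18.5% | 42/151 = 27.8% | 56/151 = 37.1% |
| 31 July 2015 | 1 July 2016 | 58/181 = 32.0% | 72/181 = 39.8% | 86/181 = 47.5% |

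In the first row, 180 × 28/181 ≈ 28 and 180 × 56/181 ≈ 56 active-arm patients. With the start held at 1 February the range is 0-48%. A start on 28 February would raise the upper end to 56%.

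**The case against.** The strongest reply is that this is a condensed article. Visit windows and a control-arm anchor date are details that the full protocol often holds, so their absence is no defect. That is right as far as windows go. But the article does state the anchor, and the anchor it states is tied to an event that ITAU does not have. A nominal ITAU date in the full protocol would align the arms on average, though not patient by patient.

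Four stronger readings are tempting, and the document supports none of them.
- *The arms are compared at different times.* Nothing says that ITAU visits are timed differently. One schedule is given for all patients, and unequal timing is a possible consequence.
- *The July 2016 close cannot hold the 12-month visits.* This is true only of late recruits. Most patients fit under the main assumptions, and the dates are month-only forecasts.
- *All 240 patients are exposed to the overrun.* Only the 180 in the active arms have a programme. Counting ITAU patients as well requires a nominal programme length for them, which would also remove most of the timing gap between arms.
- *Waiting for a group adds several weeks.* The text says only that "Face-to-face session will involve 3-5 patients and will be 90 minutes in length". No wait is stated, and any figure would need a model of how groups fill. A wait would lengthen the intervals above by its own length.

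It is also fair to object that no PHQ-9 bias has been sized and no direction shown. The document gives no basis for doing either.

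**Conclusion.** The point holds in two parts. First, the anchor for every follow-up visit, including the primary PHQ-9, depends on patient pace in three arms and is undefined in ITAU and for non-completers. The arms may therefore be compared at different times, by about 4-8 weeks or 0-4 weeks according to how ITAU is dated. The effect on the PHQ-9 contrast is unknown.

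Second, the schedule does not fit the forecast dates or the 12-month horizon. About 15-31% of active-arm patients would reach 12 months post-treatment after the close. That figure rests on uniform accrual from 1 February to 31 July 2015, a close on 31 July 2016 and no wait before the programme starts. It is sensitive to how the month-only dates are read.

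**What to change.** Schedule all assessments in all four arms at fixed times from randomisation: one fixed week set after the expected end of the programme, then 6 and 12 months from randomisation. Collect them whether or not the modules are finished. Use the same wording in Instruments, Table 1 and Main outcome. This agrees with the 12-month horizon and fits a close at the end of July 2016, though without slack for late completion.

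The cost is mainly wording and rescheduling, since Table 1 shows that most follow-up instruments are completed online. There are two small downsides. Slow users may be assessed before they finish. The last visit will also fall about 44-48 weeks after the programme ends (52 − 8 to 52 − 4), not 12 months after it.

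If follow-up must run from the end of treatment, give ITAU and non-completers a fixed nominal post-treatment date and move the end of monitoring to at least late September 2016, later if users are slower or wait for a group. That takes about two months from the interval before the forecast publication date of December 2016. The economic time horizon would then need to be reconciled with the visit times.
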